## Abstract

**Background:**

World Trade Center (WTC) general responders (GRs) continue to experience long-term mental health conditions, including posttraumatic stress disorder (PTSD), depression, anxiety, and sleep disturbance. A growing number of GRs reside in Florida, where barriers such as stigma, limited access to specialty care, and age-related limitations contribute to persistent unmet mental health needs. PTSD Coach, a mobile app originally developed for trauma-exposed veterans, has shown promise but has not been evaluated with WTC GRs or adapted for Spanish-speaking responders.

**Objective:**

This study aims to evaluate the feasibility, acceptability, and efficacy of Clinician-Supported (CS) PTSD Coach for reducing PTSD symptoms among English-speaking and Spanish-speaking WTC GRs living in Florida. Secondary objectives include evaluating effects on depression, anxiety, and sleep disturbance; comparing CS PTSD Coach with Self-Managed (SM) PTSD Coach and a waitlist control; and adapting and delivering a Spanish-language version of the intervention.

**Methods:**

This study is a 3-arm randomized controlled trial comparing CS PTSD Coach, SM PTSD Coach, and a waitlist control for reducing PTSD, depression, anxiety, and sleep disturbance among English-speaking and Spanish-speaking WTC GRs living in Florida. A total of 120 participants are randomized and assessed at baseline, 8 weeks, and a 12-week follow-up. CS PTSD Coach includes 4 clinician-guided sessions integrated with app-based activities, whereas SM PTSD Coach includes a single orientation session. Outcomes include PTSD symptoms (PTSD Checklist for DSM-5), depression (Patient Health Questionnaire-9), anxiety (Generalized Anxiety Disorder-7), and sleep disturbance (Insomnia Severity Index). Feasibility and acceptability are assessed using app use data, satisfaction ratings, and usability measures. Primary analyses focus on between-group differences after the intervention (8 weeks), with secondary longitudinal analyses incorporating all assessment time points.

**Results:**

The notice of award was received in September 2024, and institutional review board approval, including amendments, was granted in January 2025. Recruitment began in February 2025, with data collection initiated in March 2025. As of April 2026, 63 participants have been enrolled, and outcome data collection is ongoing. Data analysis will commence following completion of follow-up assessments, with dissemination of results anticipated in 2027.

**Conclusions:**

This trial will provide the first randomized controlled evaluation of a clinician-supported mobile PTSD intervention for WTC responders, including Spanish-speaking GRs. Findings will inform the feasibility, acceptability, and potential scalability of supported digital mental health interventions for aging, geographically dispersed disaster-exposed populations.

## Introduction

### Background and Rationale

The World Trade Center Health Program (WTCHP), funded by the Centers for Disease Control and Prevention and the National Institute for Occupational Safety and Health (NIOSH) since 2011, provides medical monitoring and treatment for September 11, 2001 (9/11)-related conditions to more than 140,000 individuals, with enrollment increasing by about 6% annually [1,2]. Research on the World Trade Center (WTC) cohort has documented WTC-related mental health conditions that include posttraumatic stress disorder (PTSD) as the most commonly certified psychiatric condition with a prevalence ranging from 3.8% to 29.6% [3], as well as anxiety, depression, substance abuse, and sleep disturbances [4,5]. Most of these conditions show a chronic or persistent course, with symptoms lasting for years after exposure. As of September 2023, the WTCHP has certified WTC-related mental health conditions in about 17% of responders and survivors [1,2].

Many general responders (GRs)—workers or volunteers involved in rescue, recovery, cleanup efforts, or related support services—experience significant symptoms of subthreshold PTSD (ie, <30 on PTSD Checklist for DSM-5 [PCL-5]) [6,7]. Overall, 26.8% of police and 46% of nontraditional responders (eg, construction and demolition workers, and volunteers) met the criteria for probable WTC-related full or subthreshold PTSD an average of 12 years after 9/11 [8]. GRs with subthreshold PTSD commonly experience significant distress and long-lasting functional impairment related to specific sets of symptoms, such as hypervigilance and avoidance [9], which highlight the need for assessment and treatment [8]. Almost 20 years after 9/11, nearly half of nontraditional responders and a fifth of police responders reported a need for mental health support [10].

However, rates of those seeking mental health services are lower than expected [11], and perceived unmet mental healthcare need is persistent [12,13]. A focus group study on WTC GRs underlined the systematic challenges to accessing mental health care [14]. Some of the challenges included stigma, lack of institutional recognition of PTSD, limited treatment options, and practical obstacles such as transportation and age-related bias. These recurring challenges underscored the study’s conclusion that responders face entrenched, system-level obstacles to obtaining needed care.

In 2012 and 2014, the WTCHP Scientific Technical Advisory Committee recommended research on mental health interventions [15] and the *“*effectiveness and utility of PTSD treatments*”* [16]. A 2020 review based on the National Institute of Environmental Health Sciences translational research framework [17] noted that although clinical interventions in the WTCHP included a wide range of options [3,18-24], there were few controlled studies. Most interventions were delivered in person with highly exposed individuals [3]. At the time this study was developed, no studies were conducted with mobile app–based remote interventions to serve the large number of GRs with full or subthreshold PTSD. Furthermore, no interventions focused on Spanish-speaking Hispanic GRs have been conducted.

Studies of PTSD interventions for which current evidence has been supportive in other populations (eg, military veterans) can be used to advance care for GRs along the translational spectrum [17]. Furthermore, WTC researchers have strongly recommended trials that include tele-mental health [17].

### Growing WTC Subcohort in Florida

The number of eligible WTCHP members relocating to Florida has steadily risen over the years. National distribution figures of WTC members with a National Providers Network assignment show Florida as the largest location [25]. Additional data from the WTCHP General Responder Data Center (GRDC) reported that 7346 GRs were registered with a Florida address in 2025 [26]. In collaboration with the WTCHP GRDC, our research group conducted a secondary data analysis of the data on GRs living in Florida in 2023. The WTC GRs in Florida, for whom monitoring data were available (N=3124), were on average aged just over 60 years (61.4, SD 8.5 years), frequently retired (n=1252, 44.6%), male (n=2292, 81.6%), and of Hispanic ethnicity (n=727, 25.9%). Some WTC GRs (n=370, 15.1%) had a WTC-related mental health condition.

In addition to the secondary data analysis, our team surveyed Florida WTC GRs in August 2023 about their research interests. A total of 244 GRs responded and expressed strong interest in PTSD and sleep-related studies (n=127, 52% and n=185, 76%, respectively). Although the preference for receiving support was for in-person interventions (n=107, 44%), 22% (n=44) of respondents expressed a preference for app-based or remote modalities, and an additional 44% (n=107) reported no opposition to their use.

This study responds to one of the research areas of the Zadroga Act (Title 42 USC §300 mm–51) to treat *“*WTC-related health conditions for which there has been treatment uncertainty*”* and, by including Spanish-speaking Hispanic GRs, helps advance health equity as required in Notice of Funding Opportunity issued by the National Institutes of Health Office of Human Resources (NOT-OH-23‐002).

The focus on this subcohort of the GRs in Florida is especially relevant, given that members generally relocate to Florida upon retirement and are older compared to GRs living elsewhere. As this subcohort continues to grow, aging may intersect with the long-term mental health effects associated with 9/11 exposures. Relocation can disrupt continuity of mental health care; embedding a supported digital intervention within the WTCHP and the National Providers Network may help sustain engagement and reduce symptoms during relocation, including among Spanish-speaking responders.

Persistent symptom burden alongside underuse of care reflects enduring barriers, including stigma, travel demands, limited specialty availability, and challenges faced by retired or older responders, such as reduced mobility and progression of medical conditions. App-based, clinician-supported care offers a scalable approach to addressing these barriers while preserving trauma-informed treatment strategies in a geographically dispersed cohort.

### Aims of the Study

The overarching goal of the study is to assess the feasibility, acceptability, and efficacy of Clinician-Supported (CS) PTSD Coach, originally developed for English-speaking military veterans [27,28] but never tested with WTCHP members, for reducing symptoms of PTSD, depression, anxiety, and sleep disturbance among multiethnic English-speaking and Spanish-speaking GRs in Florida. The four primary aims are to (1) assess the feasibility of CS PTSD Coach with GRs living in Florida; (2) evaluate the acceptability of CS PTSD Coach; (3) determine the efficacy of CS PTSD Coach in reducing PTSD, depression, anxiety, and sleep symptoms through a controlled trial; and (4) develop and deliver a Spanish-language version of CS PTSD Coach.

### Hypotheses and Exploratory Analyses

If both the CS and SM PTSD Coach interventions demonstrate improvements relative to the waitlist control, we will conduct direct comparisons between CS and SM PTSD Coach to evaluate differential symptom reduction. We hypothesize that CS PTSD Coach will result in greater reductions in PTSD, depression, anxiety, and sleep disturbance due to the addition of clinician support.

We also explore potential moderators and mediators of treatment effects, including baseline PTSD severity, sex, race, ethnicity, language, and engagement level. These analyses are exploratory and intended to inform future hypothesis-driven studies.

The fourth aim focuses on developing and delivering a Spanish-language version of CS PTSD Coach. The existing English-language clinician manual has been adapted for 9/11 responders and translated into Spanish. The adapted intervention is delivered by bilingual or bicultural clinicians, and its feasibility, acceptability, and preliminary efficacy evaluated using the same measures as the English-language intervention.

## Methods

### Study Design

The study design in the 2-year project includes a 3-arm randomized controlled trial (RCT) of the experimental intervention CS PTSD Coach, compared to Self-Managed (SM) PTSD Coach and a waitlist control, with each group assessed at baseline, immediate postintervention (8 weeks), and follow-up (12 weeks). The RCT design combines feasibility, acceptability, and efficacy based on CS PTSD Coach effectiveness with English-speaking veterans in the Department of Veterans Affairs (VA) [27,28]. Feasibility, acceptability, and efficacy data will fill the gap of knowledge on mental health interventions specifically for the WTC GRs and especially for the Spanish-speaking population. This design achieves a balance between efficacy (internal validity) and clinical utility (external validity) [29] by including an RCT and collecting data on the acceptability and feasibility of both the CS and SM versions of PTSD Coach for English and Spanish speakers. Although we predict that the CS version will be more efficacious than SM PTSD Coach, given the added support [27,30], the design also yields valuable information about 2 interventions.

In addition to efficacy and clinical utility, additional strengths include manualized treatment and theory-driven and data-driven hypotheses and treatment. Additionally, we plan to explore several potential moderators and mediators, which may predict differential treatment outcomes.

The trial was registered with ClinicalTrials.gov (NCT06648928) before participant enrollment. Protocol development and reporting followed the SPIRIT (Standard Protocol Items: Recommendations for Interventional Trials) 2013 guidelines for clinical trial protocols.

### Randomization and Groups

As indicated in Figure 1, after baseline assessment, participants are assigned based on a random number generator on a rolling basis into three groups: (1) experimental treatment CS PTSD Coach, (2) alternative treatment SM PTSD Coach, and (3) a waitlist control that receives no treatment until after the follow-up assessment. Allocation concealment is supported by using sequentially numbered, opaque, sealed envelopes prepared by an individual not involved in assessment or intervention; envelopes are opened sequentially after participant enrollment.

**Figure 1. F1:**
[figure not shown]
Study design. CS: Clinician-Supported; PTSD: posttraumatic stress disorder; SM: Self-Managed.

After assignment, participants receive CS PTSD Coach, SM PTSD Coach, or the waitlist control group. Participants in all 3 groups are assessed at 8 weeks (the typical duration of the CS PTSD Coach) and 4 weeks later at follow-up (12 weeks). At that point, participants in the waitlist control group are given the choice of CS or SM PTSD Coach but are not further evaluated. This approach was adopted for ethical reasons to provide all participants with a choice of treatment at the end.

### Participants

WTC GRs currently living in Florida, of any age, with PCL-5 scores consistent with subthreshold or clinical PTSD (eg, *>*27) are included. Participants are introduced to the project through a contact via SMS text messaging, email, or letter by the recruitment team. To be included, participants must have a smartphone capable of running PTSD Coach (available on both Android and iOS platforms) and be fluent in either English or Spanish.

Exclusion criteria determined by the initial screening with the assessors include (1) active or recent (past month) suicidal ideation or attempt; (2) severe alcohol use measured by an Alcohol Use Disorders Identification Test score of 20+ [31]; (3) except for cannabis, no use of illicit or unprescribed drugs in the last 2 weeks as indicated on the American Psychiatric Association Level 2 Substance Use Measure [32]; (4) presence of neurologic or neurodegenerative conditions associated with significant cognitive impairment measured using the Blessed Orientation-Memory-Concentration test [33]; and (5) current mental health counseling for PTSD (primary outcome) to avoid confounding effects. Participants endorsing active suicidal ideation during screening receive an immediate safety evaluation and are provided referrals to appropriate mental health services or emergency care, with follow-up outreach conducted when clinically appropriate.

### Recruitment

Recruitment benefits from the network established in an ongoing survey targeting Florida WTC GRs and is supported by bilingual outreach staff. The recruitment strategy uses two consecutive approaches: (1) direct contact via email, phone, and home address of WTCHP members who consented to be contacted for research, with information provided by the WTCHP GRDC and (2) public outreach through university and electronic releases, a website, and participation in local emergency responder events, facilitated through established contacts with WTC firefighters and law enforcement representatives residing in Florida.

### Sample Size Calculation

The rationale for selecting a sample size of 120 participants, 40 per group across the 3 arms of the RCT (CS PTSD Coach, SM PTSD Coach, and waitlist control), is based on achieving sufficient statistical power to detect meaningful differences in the outcomes. As the primary analysis is to compare the preintervention (baseline) and postintervention (8 weeks) change in outcomes across intervention arms, analysis of covariance (ANCOVA) serves as the primary between-group analytic approach as it is the most powerful model for pre- and postanalysis. Specifically, with 10% expected data attrition, this sample size will provide 80% power to detect a minimal difference of 0.30 SDs between-group means using ANCOVA with a significance level of *P*<.05. The design assumes a common within-group SD of 1.00 and covariates with an R-squared of 0.20, ensuring robust comparisons across interventions while accounting for potential confounding variables.

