#### Clinical Outcomes

The primary clinical outcome variable, PTSD symptoms, is assessed at all 3 time points (baseline, postintervention, follow-up) using the PCL-5, which has good reliability and validity [7,40]. The PCL-5 is used to assess changes in treatment response, with items rated on a 0 (not at all) to 4 (extremely) scale and higher total scores reflecting greater PTSD symptom severity. Studies of expected minimal important difference with the PCL-5 indicated that changes under 5 are unreliable and 9 to 12 points reflect real change [41]. Thus, we expect at least a 5-point difference to be reliable change and 9 to reflect clinically meaningful differences. As few PTSD Coach studies have explored changes in specific PTSD symptom clusters [38], we will conduct exploratory subscale analyses to identify which clusters respond best to the intervention.

Depression severity, a secondary clinical outcome, is assessed at all 3 time points using the Patient Health Questionnaire-9 (PHQ-9), a reliable and valid measure [42,43] used in similar studies [28,44]. The PHQ-9 is a 9-item self-report measure of depression symptoms in the past 2 weeks. Participants rate each item on a 0 (not at all) to 3 (nearly every day) scale. A score of 5 indicates mild depression, 10 to 14 moderate, 15 to 19 moderately severe, and 20 to 27 severe [43]. Scores ranging from 8 to 11 suggest major depressive disorder [45].

Anxiety, a secondary clinical outcome, often cooccurs with PTSD [37] and is assessed at the 3 time points using the Generalized Anxiety Disorder-7 (GAD-7)[46], a 7-item self-report measure of general anxiety symptoms over the past 2 weeks. Respondents rate their anxiety on a scale from 0 (not at all) to 3 (nearly every day). The measure has good reliability and validity [46,47] and has been used with first responders [44]. A score of 8 or higher indicates probable generalized anxiety disorder [48,49], with cut points of 5, 10, and 15 indicating mild, moderate, and severe levels of anxiety, respectively [46].

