### Statistical Analysis Plan

In aim 1 (feasibility), we will assess the feasibility of PTSD Coach with multiethnic GRs in Florida. App use data obtained from the VA will be summarized descriptively with mean (SD) for continuous variables (eg, time spent in the app) and frequency (N) and percent (%) for categorical variables (eg, modules completed). The use patterns will be examined by the intervention group (CS vs SM) and language (English vs Spanish) used.

In aim 2 (acceptability), we will evaluate the acceptability of the CS PTSD Coach intervention. Satisfaction is assessed using the Client Satisfaction Questionnaire, with ratings of “good” or “excellent” indicating endorsement. Acceptability and appropriateness are measured using the Acceptability of Intervention Measure and the Intervention Appropriateness Measure, with agreement ratings serving as indicators of positive reception. Data will be summarized with mean (SD) for continuous variables and frequency and percent for categorical variables. The data will be summarized for the entire cohort and by both intervention and language groups.

In aim 3 (efficacy), we will evaluate the efficacy of CS PTSD Coach in reducing symptoms of PTSD, depression, anxiety, and sleep disturbance when compared with SM PTSD Coach and the waitlist control group. Changes in symptoms are measured using the PCL-5 for PTSD, PHQ-9 for depression, GAD-7 for anxiety, and ISI for sleep disturbance. Exploratory analyses will assess the responsiveness of specific PTSD symptom clusters to the 2 interventions [38]. Within-group changes will be summarized descriptively (mean change and 95% CIs) to aid interpretation.

The primary analysis will compare postintervention (8 weeks) outcomes between intervention groups using ANCOVA, adjusting for baseline outcome values and prespecified covariates (eg, language group). The primary estimand is the between-group difference in change from baseline to 8 weeks.

Separate ANCOVA models will be done to compare between-group changes from baseline to 12-week follow-up (secondary analysis) and from postintervention to 12-week follow-up (exploratory analysis). The sample size and power calculations are applicable to all ANCOVA models.

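### The stated 80% power for a 0.30 SD difference between arms is wrong: the stated inputs give about 29%, and 80% power is reached only at about 0.60 SD

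*Protocol article*

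**What the plan says.** The Sample Size Calculation section of the protocol article justifies "a sample size of 120 participants, 40 per group across the 3 arms of the RCT". Allowing for a 10% loss of data and testing at the 0.05 level, it claims that "this sample size will provide 80% power to detect a minimal difference of 0.30 SDs between-group means using ANCOVA". On the remaining inputs the section says: "The design assumes a common within-group SD of 1.00 and covariates with an R-squared of 0.20".

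The Statistical Analysis Plan section describes the test this is meant to power: "The primary analysis will compare postintervention (8 weeks) outcomes between intervention groups using ANCOVA, adjusting for baseline outcome values and prespecified covariates". It also says: "The primary estimand is the between-group difference in change from baseline to 8 weeks". The same section extends the power calculation to every ANCOVA in the plan, which includes the models for the 12-week follow-up.

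**The concern.** Thirty-six participants per arm is a small group for a between-arm difference of 0.30 SD, and an R-squared of 0.20 shrinks the residual SD by only about 11%. An 80% power claim on those inputs looks implausible at first sight.

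The claim is the whole justification for the sample size, and it sets what readers will expect the trial to detect. The Hypotheses section plans a direct comparison of the clinician-supported and self-managed arms, conditional on both improving on waitlist. Those two active arms differ in the amount of clinician support, so a modest difference is plausible. If the trial is believed to be sensitive to 0.30 SD, a null result there could be read as showing that clinician support adds little, when the trial could not have shown otherwise.

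**Working it through.** **Inputs (Sample Size Calculation section)**

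- 40 randomised per arm and 10% attrition: n = 40 × 0.90 = 36 per arm, N = 108.
- SD 1.00 and R² = 0.20: residual SD = √(1 − 0.20) = 0.894.
- Significance level 0.05. Sidedness is not stated, so two-sided is assumed and one-sided is tried as well.

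**Attempt to reproduce the stated 80% (pairwise contrast)**

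- Standard error = 0.894 × √(2/36) = 0.211.
- Normal approximation: 0.30/0.211 − 1.960 = 1.423 − 1.960 = −0.537, so power = Φ(−0.537) = 0.296.
- Noncentral t with noncentrality 1.42: power 0.291 on 104 df (error term pooled over three arms) and 0.289 on 69 df (two arms only).

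The stated figure is not reproduced.

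**Difference detectable with 80% power**

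- Normal approximation: (1.960 + 0.842) × 0.211 = 0.591 SD.
- Noncentral t: 0.596 SD (104 df) or 0.599 SD (69 df).

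**What 0.30 SD would require**

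- Sample size: n = 2 × 0.80 × (1.960 + 0.842)² / 0.30² ≈ 140 evaluable per arm. Then 140/0.90 = 155.6, so 156 randomised per arm, or 468 in total.
- Or, keeping 36 per arm: R² = 1 − [0.30 / (2.802 × √(2/36))]² = 0.794, against the stated 0.20 (0.797 with the t distribution).

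**Other readings of the sentence**

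The omnibus rows use a noncentral F on 2 and 104 df, with λ = N f²/(1 − R²), where f² is the variance of the three arm means in SD units.

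| Reading | Power |
|---|---|
| Pairwise, no attrition (40 per arm) | 0.32 |
| Pairwise, one-sided, 36 per arm | 0.41 |
| Pairwise, one-sided, 40 per arm | 0.44 |
| Both active arms pooled against waitlist (72 vs 36) | 0.38 |
| Omnibus, largest gap 0.30, third mean midway (f² = 0.015, λ = 2.03) | 0.22 |
| Omnibus, largest gap 0.30, two arms equal (f² = 0.020, λ = 2.70) | 0.29 |
| Omnibus, arms at 0, 0.30 and 0.60 (f² = 0.060, λ = 8.10) | 0.71 |
| Omnibus, Cohen's f = 0.30, R² ignored (λ = 9.72) | 0.79 |
| Omnibus, Cohen's f = 0.30, R² = 0.20 (λ = 12.15) | 0.88 |

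The f detectable with 80% power at N = 108 is 0.303 without the covariate gain and 0.271 with it. An f of 0.30 corresponds to a largest gap of 0.30 × 3/√2 = 0.64 SD if two arms are equal, or 0.30 × √6 = 0.73 SD if the arms are evenly spaced. With R² = 0.20, f = 0.271 corresponds to 0.57 to 0.66 SD.

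**In PCL-5 points**

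The article gives no PCL-5 SD. For an assumed SD of 12 to 16, 0.30 SD is 3.6 to 4.8 points, and 0.596 SD is 7.2 to 9.5 points. A difference of 0.30 SD reaches 5 points only if the SD is at least 5/0.30 = 16.7.

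**The case against.** The strongest reply is that the article does not say whether the primary test is pairwise or omnibus, and that 0.30 fits the omnibus test if it is Cohen's f. There is something in this: the 79% at N = 108 is close to the claim. But it requires ignoring the R-squared that the same paragraph states (with it, power is 88%). It also requires reading a difference between means as an SD of means. The sentence and the primary estimand both speak of between-group differences. That f was the source remains an inference; that the sentence is wrong as written does not depend on it.

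A second reply takes 0.30 SD as the smallest gap between three ordered arms. That gives 71% (76% with all 120 evaluable), still short of 80%. The largest gap is then 0.60 SD, and the article does not describe this pattern.

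Two cautions do stand. First, the Clinical Outcomes benchmark, that "changes under 5 are unreliable and 9 to 12 points reflect real change", concerns change in scores, so setting it beside a difference between arm means is orientation only. Second, the PCL-5 SD is an assumption, and no multiplicity adjustment is stated. Purely for illustration, a Bonferroni level of 0.05/3 would lower pairwise power at 0.30 SD to about 16% and raise the detectable difference to about 0.70 SD. None of this affects the central calculation.

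**Conclusion.** The concern holds. On the article's own inputs, with two-sided testing as the one added assumption, power for a 0.30 SD pairwise difference is about 29%, not 80%, and the 80% detectable difference is about 0.60 SD. The stated sensitivity is too favourable by a factor of two, and a true 0.30 SD benefit would be missed about 7 times in 10. A one-sided test does not change the conclusion (41% power; detectable difference 0.53 SD). Because the power statement is extended to all ANCOVA models, the error carries over to the secondary and exploratory comparisons.

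This must be corrected, but it does not condemn the design. Under the assumed PCL-5 SD of 12 to 16, the difference the trial can detect is near the 9-point benchmark that the article itself calls clinically meaningful.

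**What to change.** Keep N = 120 and correct the Sample Size Calculation section, for example:

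> With 36 evaluable participants per arm, two-sided alpha 0.05 and R-squared 0.20, the trial has 80% power for a pairwise difference of about 0.60 SD; power for 0.30 SD is about 29%.

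If the omnibus test was intended, say so. Give the effect size as Cohen's f (0.27 with R-squared 0.20, 0.30 without) together with the pairwise differences it implies. In either case, add the equivalent in PCL-5 points, with the assumed SD stated, beside the 5- and 9-point benchmarks. Bring the sentence that applies the calculation to all ANCOVA models into line, and correct the SAP if it repeats the figure.

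The cost is one paragraph of wording and a less favourable stated sensitivity. No extra patients are needed. According to the Results section, analysis begins only after follow-up is complete, so the correction can be made before any outcome is analysed.
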